## Abstract

**Background:**

Management of localized renal cell carcinoma (RCC) is challenged by inaccurate methods to assess the risk of recurrence and deferred detection of relapse and residual disease after radical or partial nephrectomy. Circulating tumor DNA (ctDNA) has been proposed as a potential biomarker in RCC.

**Purpose:**

Conduction of an observational study to evaluate the validity of ctDNA as a biomarker of the risk of recurrence and subclinical residual disease to improve postoperative surveillance.

**Material and methods:**

Urine and blood will be prospectively collected before and after surgery of the primary tumor from up to 500 patients until 5 years of follow-up. ctDNA analysis will be performed using shallow whole genome sequencing and cell-free methylated DNA immunoprecipitation sequencing. ctDNA levels in plasma and urine will be correlated to oncological outcomes. Residual blood and urine as well as tissue biopsies will be biobanked for future research.

**Interpretation:**

Results will pave the way for future ctDNA-guided clinical trials aiming to improve RCC management.

## Background

### Treatment of localized renal cancer

Localized renal cell carcinoma (RCC) is treated with partial or radical nephrectomy, or ablation therapy with curative intent. After surgery, patients with stage I–III RCC are offered a watchful waiting program depending on the given risk assessment. The postoperative follow-up scheme in Denmark relies on the Leibovich score which divides patients into ‘low’, ‘intermediate’, and ‘high’ risk groups. Based on this risk assessment, patients are offered computerized tomography (CT) scans at set intervals [1]. However, especially the ‘intermediate’ risk group constitutes a clinical challenge and could benefit from a refinement to identify which patients are most likely to relapse. In Denmark, roughly 25% of patients in the ‘intermediate’ risk group will relapse within 5 years, while the number is ~50% for the ‘high’ and ~10% for the ‘low’ risk group patients [2]. Thus, the current risk stratification is not optimal to identify patients with the highest risk of relapse after treatment of localized RCC.

Disease recurrence is closely linked to minimal residual disease (MRD) [3], thus detection of MRD early is critical for a successful treatment. However, no detection method for MRD is currently used in routine clinical practice [1], since small lesions and MRD might be undetectable with current imaging modalities which can only detect cancer nodules above a given size. Thus, there is a need for novel methods suitable for MRD detection.

### The potential of circulating tumor DNA in renal cancer management

Solid tumors, including RCC, release DNA fragments into the circulation. The tumor-derived part of the cell-free DNA (cfDNA), that circulates in biological fluids of cancer patients, is referred to as circulating tumor DNA (ctDNA). The half-life of cfDNA is short (<2 h) [4], enabling real-time characterization of tumor burden, with detection of ctDNA postoperatively indicating residual disease or occult dissemination of cancer cells prior to surgery.

Earlier studies have proposed cfDNA/ctDNA as a prognostic biomarker and a monitoring tool in RCC (reviewed in [5]). Until recently, ctDNA assays were challenged by the trace amounts of ctDNA shed by RCC [5, 6]. However, with the new more sensitive method cell-free methylated DNA immunoprecipitation-sequencing (cfMeDIP-seq) it is now feasible to study ctDNA in patients with RCC [7].

### Rationale

The hypothesis of the KIDNEY-PAGER study is that ctDNA detected before and/or after intended curative treatment for localized RCC can be utilized as a biomarker predicting higher risk of recurrence, indicating subclinical MRD, and as a sensitive tool for monitoring recurrence during postoperative surveillance.

### Aims and objectives

The overall aim of this protocol is to conduct an observational study to confirm that ctDNA detected in plasma and/or urine after treatment for RCC with curative intent can be applied in clinical practice as a biomarker of subclinical MRD and risk of recurrence. Thus, this study aims to pave the way for future ctDNA-guided clinical trials with the aim of improving postoperative surveillance and treatment strategies for patients with RCC.

#### Primary objective

To confirm that patients with residual disease and a high risk of recurrence can be identified with ctDNA profiling performed immediately after nephrectomy.

#### Secondary objectives

To apply ctDNA pre- and post-operatively as a risk stratification tool.To validate the potential of a ctDNA-guided follow-up scheme compared to the current follow-up scheme with frequent CT scans after surgery.To investigate a possible lead-time between *molecular* recurrence (detected using serial plasma and urine ctDNA analyses) and *clinical* recurrence (detected using radiological examinations).To find and validate prognostic and predictive blood-based biomarkers for immunotherapy and/or targeted therapies by correlating ctDNA levels with oncological outcome parameters.To confirm that changes in ctDNA levels reflect the therapeutic effect of the given therapy.To delineate markers of tumor aggressiveness and compare them to ctDNA measurements.

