## Material and methods

### Study design

This study is based on a prospective collection of blood and urine samples for ctDNA analysis before and after surgery of localized RCC and during postoperative surveillance (Figure 1). Included patients are in the project followed until the 5-year scheduled follow-up CT scan.

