**Figure 1 F0001:**
[figure not shown]
Study design. Blood (plasma and buffy coat), urine, and tumor tissue will be collected as indicated during patient management. CT: computed tomography; pre-OP: preoperatively; post-OP: postoperatively; RCC: renal cell carcinoma. Figure is created with BioRender.com.

Urine and blood samples for ctDNA analysis were taken preoperatively and approximately 2 weeks after surgery.Sampling of tissue from the resected tumor specimen as well as adjacent normal kidney.Longitudinal blood and urine sampling is contemporary with follow-up abdominal and thoracic CT scans, and with oncological treatment if metastatic disease is diagnosed. If relapse occurs, tissue from metastatic lesions will be obtained if possible.

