### Experimental plans and statistically analysis

ctDNA will be detected and measured before and after surgery using shallow whole genome sequencing (sWGS) and cfMeDIP-sequencing [8]. ctDNA levels will be estimated from sWGS data by the assessment of copy number profiles. Enrichment data from cfMeDIP-sequencing will be transformed into methylation levels and normalized to copy number variants in the sWGS data. Differentially methylated regions will be called whereafter a classifier will be built using machine learning methods. ctDNA levels will be estimated from methylation data by assignment of a methylation score to each patient sample based on the established classifier. ctDNA detection will be correlated with time to relapse, progression-free survival, time to subsequent systemic therapy, and overall survival, using statistical methods (e.g. Cox regression). Moreover, ctDNA levels will be measured longitudinally during surveillance to detect relapses. ctDNA detection will be correlated with the clinical detection of relapse using CT scans, and if applicable, lead time between molecular recurrence and clinical recurrence will be calculated.

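### Correlating ctDNA with outcome in one observational cohort cannot tell a predictive marker from a prognostic one, so the secondary objective on predictive biomarkers cannot be met by the method it names

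*Protocol article*

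**What the plan says.** The protocol article, under Secondary objectives, includes this aim: "To find and validate prognostic and predictive blood-based biomarkers for immunotherapy and/or targeted therapies by correlating ctDNA levels with oncological outcome parameters". The goal and the method stand in the same sentence.

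The design is described elsewhere in the article:

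- Aims and objectives: "The overall aim of this protocol is to conduct an observational study".
- Study design: "This study is based on a prospective collection of blood and urine samples for ctDNA analysis before and after surgery of localized RCC". No allocation of treatment and no control group is described.
- Figure 1 legend: blood and urine are also sampled "with oncological treatment if metastatic disease is diagnosed", so systemic therapy is part of care and is not assigned by the study.
- Experimental plans and statistically analysis: "ctDNA detection will be correlated with time to relapse, progression-free survival, time to subsequent systemic therapy, and overall survival, using statistical methods (e.g. Cox regression"). The explanatory variable is ctDNA. No treatment variable or ctDNA-by-treatment term is named.

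**The concern.** The objective lists prognostic and predictive as two things, so predictive has to mean more than association with outcome. In standard usage a prognostic marker separates patients by outcome whatever treatment they receive, and a predictive marker separates them by how much a treatment helps. The second is a statement about effect modification. It needs outcomes by marker level under at least two treatment conditions.

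The stated method looks at marker level against outcome and stops there. If a clear association appeared in patients on immunotherapy or targeted therapy, the objective's wording would invite calling ctDNA a predictive marker for those drugs, although the data could not show it. The study is meant to prepare for ctDNA-guided trials of surveillance and treatment strategies, and a mislabelled marker could misdirect their design.

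**Working it through.** **The plan's own figure.** The only sample-size figure is the accrual ceiling: up to 100 patients a year × 5 years = 500, which agrees with the stated maximum. No power, significance level or effect size is attached to this objective, so there is nothing further to reproduce. The question is one of identifiability.

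**Algebra.** Let *p* be the hazard ratio of marker-positive to marker-negative patients without the treatment (the prognostic effect). Let *t₊* and *t₋* be the treatment hazard ratios in marker-positive and marker-negative patients.

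- Marker hazard ratio among treated patients = *p* × (*t₊* / *t₋*).
- Marker hazard ratio among untreated patients = *p*.
- Interaction (the predictive effect) = *t₊* / *t₋* = the first divided by the second.

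A treated-only analysis gives one number for a product of two unknowns.

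**Two opposite cases (effects assumed).**

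| Case | *p* | *t₊* | *t₋* | Marker HR, treated only | Interaction |
|---|---|---|---|---|---|
| Purely prognostic | 2.0 | 0.6 | 0.6 | 2.0 × 0.6/0.6 = 2.0 | 0.6/0.6 = 1.0 |
| Purely predictive | 1.0 | 1.2 | 0.6 | 1.0 × 1.2/0.6 = 2.0 | 1.2/0.6 = 2.0 |

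**Simulation check.** Survival was exponential with 50% marker prevalence, no censoring and 2,000 runs. The sizes 50, 125 and 250 treated patients are 500 × 10%, 25% and 50%, the 5-year relapse rates that the Background gives for the low, intermediate and high risk groups. They serve only to span a range.

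- Purely prognostic marker: treated-only hazard ratio about 2.0, significant in 69%, 97% and over 99% of runs.
- Purely predictive marker: treated-only hazard ratio about 2.0, significant in 69%, 97% and 100% of runs.
- With an equally large, comparable untreated group added, the estimated interaction was about 1.0 in the first case and about 2.0 in the second.

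The planned correlation gives the same answer in both cases at every size. Only the comparison group separates them.

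**What an interaction would demand (illustration, not needed for the point).** For two-sided 5% significance, 80% power and balanced groups, (1.96 + 0.84)² ≈ 7.85.

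- Marker main effect: events = 4 × 7.85 / (ln HR)². HR 2.0 needs 66 events and HR 1.5 needs 191.
- Interaction in a balanced two-by-two layout: events = 16 × 7.85 / (ln ratio of HRs)². A ratio of 2.0 needs about 262 events and a ratio of 1.5 about 764.

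An interaction therefore needs four times the events of a main effect of the same size. The document does not say how many patients will receive systemic therapy, so these counts cannot be set against an expected number.

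**The case against.** The strongest reply is that the article leaves the analysis open. Cox regression is given only as an example, and a Cox model can carry a marker-by-treatment term. The objective names two drug classes, so a contrast between them is possible in principle, and the analysis plan is not shown. The Discussion is also cautious: it says that the benefit of adjuvant therapy in low-stage ctDNA-positive patients needs randomised trials, and it treats ctDNA as a supplement to imaging at first.

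Part of this stands. A between-class interaction could be estimated. It would show prediction of one class relative to the other, and it would be open to confounding by indication. But the objective does not leave its method open: it says that the markers are to be found and validated by correlation with outcome. An analysis plan can add detail to a method, but here the named method does not address the named goal. The cautions in the Discussion concern adjuvant use and surveillance and do not qualify this objective.

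Three stronger readings are tempting and are not supported:

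- *That the correlation can show only prognosis.* The second case above refutes this: a marker with no prognostic effect still gives a hazard ratio of 2.0 among treated patients. The association mixes the two effects.
- *That discovery and validation will use the same patients.* The text says "Differentially methylated regions will be called whereafter a classifier will be built using machine learning methods", and the article describes no separate validation set. It does not say that there is none, and a full protocol could define a split.
- *That the treated patients are only those who relapse.* The inclusion criteria also admit patients with metastatic disease who are disease-free after surgery and local treatment. Adjuvant pembrolizumab was awaiting approval in Denmark, with inclusion expected to run to 2028, so later adjuvant exposure cannot be excluded.

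**Conclusion.** The point holds in a limited form. With one observational cohort and clinically chosen treatment, an association between ctDNA and outcome among treated patients would not support a claim that ctDNA predicts benefit from immunotherapy or targeted therapy. This follows from the objective's own wording and the design as described, and it does not depend on sample size. The hazard ratios, marker prevalence and numbers treated in the check are assumptions that illustrate the argument.

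The reach is modest. It concerns one part of one secondary objective. The primary objective, the sampling scheme and the prognostic half of the same objective are untouched. If predictive was meant loosely, as associated with outcome on therapy, the text should say so. It is worth correcting because the change is small and it prevents a wrong conclusion.

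**What to change.** Restrict this objective to the prognostic association of ctDNA with outcome before and during systemic therapy.

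If the predictive aim is kept, state the analysis that would address it: a ctDNA-by-treatment interaction (for example by drug class), adjusted for baseline risk and reported with its confidence interval. Label it exploratory and hypothesis-generating because treatment is not randomised, and do not describe the result as validated.

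The change is to wording in the protocol and the analysis plan. It needs no additional patients or samples, and it can be made before results are reported. The cost is a more modest secondary claim.

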## Material and methods

### Study design

This study is based on a prospective collection of blood and urine samples for ctDNA analysis before and after surgery of localized RCC and during postoperative surveillance (Figure 1). Included patients are in the project followed until the 5-year scheduled follow-up CT scan.

**Figure 1 F0001:**
[figure not shown]
Study design. Blood (plasma and buffy coat), urine, and tumor tissue will be collected as indicated during patient management. CT: computed tomography; pre-OP: preoperatively; post-OP: postoperatively; RCC: renal cell carcinoma. Figure is created with BioRender.com.

Urine and blood samples for ctDNA analysis were taken preoperatively and approximately 2 weeks after surgery.Sampling of tissue from the resected tumor specimen as well as adjacent normal kidney.Longitudinal blood and urine sampling is contemporary with follow-up abdominal and thoracic CT scans, and with oncological treatment if metastatic disease is diagnosed. If relapse occurs, tissue from metastatic lesions will be obtained if possible.

### Study population and eligibility criteria

During the inclusion period, we will prospectively include patients treated for RCC with curative intent at Aarhus University Hospital (AUH), Denmark. In total, a maximum of 500 patients operated for RCC will be included with the expectation of up to 100 patients being included per year for 5 years. The following eligibility criteria will be applied:

#### Inclusion criteria

Patients diagnosed with a locoregional renal cancer are eligible for surgical excision with curative intent and with sufficient performance status for surgery.Patients with metastatic disease, but no evidence of disease after surgery and local treatment of metastases.Patients aged 18 years or older.Patients must able to understand and sign written informed consent.

#### Exclusion criteria

Patients with local disease who are not being offered surgical treatment, including ablation therapy.Patients who are unlikely to comply with the protocol (e.g. uncooperative attitude), inability to return for subsequent visits, and/or otherwise considered to be unlikely to complete the study by the investigator.

### Recruitment and patient consent

Patients are approached in person at the treating Department of Urology, AUH. Here, patients are given written information regarding the project from which they can give informed consent. Furthermore, as the project involves genomic sequencing, which may disclose genetic variants predisposing to specific diseases, participants are given the opportunity to refuse information upon findings of special germline variants. The informed consent may be withdrawn at any time without having any impact on current or future treatment. This study will not present any personal data in any way and will not require consent for publication by any participant.

### Status

Inclusion began in June 2023 and is expected to end in 2028. The primary endpoint will be reached and ready for publication in 2031. The planned 5 years of follow-up will be complete and available for all patients by 2033. The study has been registered in the Clinical Trials database: NCT06145139.

### Sample collection

All patients will have one blood sample drawn prior to and post-surgery. The latter will take place when the patients visit the Urological Department to get the results from the histopathological examination of the resected tumor, usually on day 14. Additional blood samples will be drawn longitudinally during the postoperative follow-up period simultaneously with the planned CT scans (the number and timing of scans depends on the assigned risk group). Additionally, all patients will be asked to give a urine sample on the same dates as blood samples are drawn.

Whenever possible, fresh tumor and adjacent normal parenchyma biopsies will be collected from the surgical specimen.

### Experimental plans and statistically analysis

ctDNA will be detected and measured before and after surgery using shallow whole genome sequencing (sWGS) and cfMeDIP-sequencing [8]. ctDNA levels will be estimated from sWGS data by the assessment of copy number profiles. Enrichment data from cfMeDIP-sequencing will be transformed into methylation levels and normalized to copy number variants in the sWGS data. Differentially methylated regions will be called whereafter a classifier will be built using machine learning methods. ctDNA levels will be estimated from methylation data by assignment of a methylation score to each patient sample based on the established classifier. ctDNA detection will be correlated with time to relapse, progression-free survival, time to subsequent systemic therapy, and overall survival, using statistical methods (e.g. Cox regression). Moreover, ctDNA levels will be measured longitudinally during surveillance to detect relapses. ctDNA detection will be correlated with the clinical detection of relapse using CT scans, and if applicable, lead time between molecular recurrence and clinical recurrence will be calculated.

### Biobanking and collection of clinical information

The collection of samples is performed in collaboration with the Bio- and Genome Bank Denmark (RBGB). Residual blood, urine, and tissue biopsies as well as clinical and sequencing data will be transferred to the Renal Cancer Research Biobank at AUH for future research. The material in the research biobank will be saved and stored in a pseudonymised form at the Department of Molecular Medicine, AUH in Denmark. The samples will be marked with a unique patient number, and only the project responsible will be able to connect this number with the patient social security number. A central part of the project involves comparison and correlation of ctDNA assessments (gathered from the blood and urine samples) with the clinical information on treatment and outcome. Therefore, clinical information regarding the treatment and outcome of the treatment will be collected from hospital records and health registries; specifically, information about surgical intervention, pathology reports, biomarkers of inflammation, biomarkers of kidney function, oncological intervention, and radiological evaluations aiming at detecting disease recurrence or assessing changes in tumor burden during surveillance and treatment. Moreover, results from blood analyses will be noted.

### Ethical considerations

The ethical concerns and risks related to this study are limited. Blood sampling is associated with minimal risk and discomfort to the patient. Urine sampling is safe for the patient. Tissue samples are collected from the specimens that are resected as part of the standard treatment of the patients or to confirm disease recurrence. Hence, these biopsies introduce no additional risk to patients.

### Publication policy

Positive, negative, and non-definable findings from KIDNEY-PAGER will be published in peer-reviewed scientific journals.

## Discussion

Identifying patients with a greater risk of relapse after surgery for localized RCC could improve oncological outcomes. Recurrence usually occurs within 3 years of surgery [9], and currently the Leibovich score is used in Denmark for risk assessment. However, the current risk assessment is not sufficient to identify patients with the highest risk of relapse after surgery for localized RCC as patients across all three risk groups develop disease recurrencies [2, 10]. To improve monitoring of recurrencies, we suggest analyzing ctDNA in the management of RCC. A study from 2020 revealed the ability of detecting ctDNA across all RCC stages upon the use of the sensitive enrichment-based cfMeDIP-seq technique, despite the low amount of ctDNA shed from RCC [7].

The expected outcome of KIDNEY-PAGER is an assessment of the validity of ctDNA-based analysis to provide a more tailored postoperative follow-up scheme for RCC patients who had undergone surgery for localized RCC with curative intent. If positive for ctDNA, patients may benefit from a closer follow-up scheme regardless of the Leibovich score or would even need an immediate intervention, such as adjuvant therapy. On the contrary, surveillance, including serial ctDNA analyses instead of regular scans, could potentially be sufficient for ctDNA-negative patients, and this could consequently prevent unnecessary use of imaging resources as well as save the ctDNA-negative patients from needless worries. Yet, caution is essential to mitigate the risk of false negatives arising from technical challenges like minimal shedding from tumors. Therefore, it is advisable to consider ctDNA primarily as a supplementary tool to complement radiological evaluations in the initial stages.

Naturally, given the recent approval of pembrolizumab by the European Medicines Agency (EMA) as an adjuvant treatment for adult patients with RCC at intermediate-high or high risk of recurrence after nephrectomy, or following nephrectomy and the complete resection of metastatic lesions, ctDNA could potentially be used to stratify patients for adjuvant treatment. Yet the approval of pembrolizumab is still pending in Denmark. ctDNA analysis can further enable the improvement of factors associated with suboptimal surgery as well as the identification of patients having MRD who may benefit from adjuvant therapy but are left untreated today (stages I, II, III). The clinical benefit of treating low stage ctDNA-positive patients with adjuvant therapy needs to be further studied in randomized clinical trials.

In addition to the more accurate assessment of risk for relapse after surgery, the clinical implication of ctDNA monitoring could be the early detection of clinical relapses and residual disease while the lesions are small and potentially responsive to local or systemic therapies. This will potentially improve the disease-specific survival of patients with RCC in the future.

